### Economic evaluation

This study investigates the efficiency of the care program AID compared to usual care as provided in NH units. If the program AID turns out to be successful, a decrease in the prevalence of depression in NH will occur. On the one hand the program needs investment in for example training of nursing staff and, consequently, generates extra costs compared to usual care. On the other hand it potentially generates savings as it reduces depression related time investment in NH.

The economic evaluation is based on the general principles of a cost-effectiveness analysis from a healthcare viewpoint. Based on the above mentioned primary outcomes, two different incremental cost effectiveness ratios (ICERs) will be computed, answering the questions: 'How much money has to be invested additionally in the care program to gain one percentage point decrease in frequency of depression?' and 'How much money has to be invested additionally in the care program to gain one Quality-Adjusted Life Year (QALY)?'

The cost analysis consists of two main parts. First, on resident level, volumes of care (to determine the incremental direct health care costs) based on the production process of the care program and of depression decrease are measured prospectively using an activity based costing approach. Focusing on activities performed with costs accumulated at the activity level(s) of the health care production processes, standardized case report forms are used to assess time invested by nursing staff, psychologist, elderly care physician and recreational therapist. Also, number of hospital admissions (number of days in hospital) and use of antidepressant medication are recorded.

Second, the cost prices for each volume of consumption will be determined to use these for multiplying the volumes registered for each participating resident. The Dutch guidelines for cost analyses will be used [51]. For units of care/resources where no guideline or standard prices are available, real cost prices will be determined. Statistics of the total costs per resident will be determined for usual care and care according to the care program AID. Depending on the skewness of the parameter distributions, statistical testing of differences between strategies will be of a parametrical or non parametrical nature. The impact of deterministic variables, such as cost prices for volume parameters that are incremental cost drivers will be investigated using sensitivity analyses on the basis of the range of extremes.

The effect analysis adheres to the design of the study. Relevant for the economic evaluation are the frequency of depression (measured with GDS-8 and CSDD) and QALYs (utilities measured with the EQ-5D). Using the trapezium rule, the QALYs will be computed in order to perform a cost-effectiveness analysis comparing the two alternative strategies. Change in utilities (EQ-5D) will be based on the mean values for the residents when they are in the control condition and the mean values after having been in the intervention for 3 (all 5 groups), 7 (4 groups), 11 (3 groups), 15 (2 groups) and 19 months (1 group). ICERs will be computed and sampling uncertainty will be determined using the bootstrap or Fieller method. Finally, a cost-effectiveness acceptability curve will be derived that is able to evaluate efficiency by different thresholds for the ICERs.

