**Figure 1 F1:**
[figure not shown]
**Graphical representation of the stepped wedge design**. '0' represents measurement of usual care; control condition '1' represents measurement after the intervention has been implemented; intervention-condition

At the start of the data collection, the residents with informed consent of all 28 units are screened for depression (T0). Following this, each of the units is randomly assigned to one of 5 groups. Each group starts the intervention at different time points, directly after one of the measurements (T0-T4), which are each 4 months apart. In the four- month interval between T0 and T1, nursing staff of the first group is trained within the first month. After this month, the intervention runs for the subsequent 3 months in the first group before the second measurement (T1) of all 28 units takes place. After T1, the second group is trained, and the intervention starts in this group while it is continued in the first group. This procedure is repeated for the remaining 3 groups until, at the last measurement (T5), all 28 units are in the intervention condition. Consequently, the follow up in the intervention condition varies from 3 months for the last group, which starts with the intervention 1 month after T4, to 19 months for the first group, which starts after T0.

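### The skewness-driven choice of cost test can put the reported cost comparison at odds with the mean-based ICERs, and the cost totals per resident are given no time base

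*Protocol article*

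**What the plan says.** All references are to the protocol article.

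- **Cost quantity** (Economic evaluation): "Statistics of the total costs per resident will be determined for usual care and care according to the care program AID". No time unit or common horizon is attached to these totals.
- **Cost test** (Economic evaluation): "Depending on the skewness of the parameter distributions, statistical testing of differences between strategies will be of a parametrical or non parametrical nature".
- **What the ICERs ask** (Economic evaluation): extra money per percentage point fall in depression frequency and, in the second question, "How much money has to be invested additionally in the care program to gain one Quality-Adjusted Life Year (QALY".
- **ICER uncertainty** (Economic evaluation): "ICERs will be computed and sampling uncertainty will be determined using the bootstrap or Fieller method".
- **Design** (Methods/Design, text with Figure 1): "each of the units is randomly assigned to one of 5 groups". Each group starts "directly after one of the measurements (T0-T4), which are each 4 months apart". In the first interval, "nursing staff of the first group is trained within the first month", and the programme then runs for three months before the next measurement. As a result, "the follow up in the intervention condition varies from 3 months for the last group", and it reaches 19 months for the first.
- **Link to the design**: Data-analysis assigns multilevel regression to the primary effects and refers the reader to Economic evaluation for costs. There, the effect analysis is said to follow the study design. No matching statement is made for costs.

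**The concern.** There are two separate problems.

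**The test rule.** Both ICER questions concern additional money spent, so their numerator is a difference in arithmetic mean cost. The recorded components include hospital days and staff time in a stepped-care programme. These are likely to be low for most residents and high for a few, so the non-parametric branch is the likely one. A rank test responds to whether one distribution tends to lie above the other, not to the difference in means. The paper could then report a significant cost difference beside an ICER with almost no incremental cost, or no significant difference beside a substantial one. The rule is stated in the text, so this is not a matter of detail left to a fuller document.

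**The time base.** In a stepped wedge, time in each condition differs by group, and condition is tied to calendar time. A total per resident by condition is interpretable only if put on a common time base, and a plain comparison of strategies would allow for neither unit nor period. Cost-effectiveness is part of the study's stated aim, so the cost comparison matters.

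**Working it through.** **1. Time in each condition, by group.** Inputs are five groups, measurements four months apart and one training month per group (Methods/Design). Group k starts after T(k−1), so:

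- AID months = 4 × (6 − k) − 1, giving 19, 15, 11, 7, 3.
- Usual-care months before training = 4 × (k − 1), giving 0, 4, 8, 12, 16.

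The AID months reproduce the article's own durations for the utilities: 3 months in five groups, 7 in four, 11 in three, 15 in two and 19 in one.

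**2. Ratio of mean time, AID to usual care.** This is also the ratio of mean totals if monthly costs were identical and totals were not standardised. The article gives no group sizes. I assume equal groups, or 14 units of one type with four groups of 3 and one of 2.

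*Training month in neither condition, group 1 counted as zero usual-care months:*
- Equal groups: 11/8 = 1.375.
- 3/3/3/3/2: AID 162/14 = 11.57, usual care 104/14 = 7.43, ratio 1.56.
- 2/3/3/3/3: 146/120 = 1.22.

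*Training month in neither condition, usual-care mean taken only over groups 2 to 5, which have usual-care time after T0:*
- Equal groups: 11/10 = 1.10.
- 3/3/3/3/2: 11.57/(104/11) = 11.57/9.45 = 1.22.
- 2/3/3/3/3: (146/14)/(120/12) = 10.43/10 = 1.04.
- 3/2/3/3/3: (150/14)/(116/11) = 10.71/10.55 = 1.02.

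*Training month counted as usual-care time (one month added to every group):*
- Equal groups: 11/9 = 1.22.
- 3/3/3/3/2: 162/118 = 1.37.
- 2/3/3/3/3: 146/134 = 1.09.

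*Training month counted as AID time, group 1 as zero:*
- Equal groups: 12/8 = 1.50.
- 3/3/3/3/2: 176/104 = 1.69.

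The main cases therefore span about 1.04 to 1.56, and the extremes are 1.02 and 1.69. Every case exceeds 1, but the size depends heavily on choices the article does not state. Residents also enter during the study (Sampling), so an individual's time need not equal the group's window. With costs per resident-month, identical monthly costs give a ratio of 1.00 under every convention.

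**3. Rank test against a test of means.** The article gives no cost distribution, so this is an illustration only: lognormal costs, independent residents, 2,000 runs per setting, two-sided 5% level, Mann-Whitney against Welch.

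- Equal means, log-SD 1.0 in both conditions: rank test 5.7% (n = 140 per condition) and 4.6% (n = 280); Welch 5.3% in both.
- Equal means, log-SD 1.0 vs 1.25: rank test 53% (n = 140) and 82% (n = 280); Welch about 6%.
- Equal means, log-SD 1.0 vs 1.5: rank test 98% and 100%; Welch 8% and 7%.
- Equal medians, log-SD 1.0 vs 1.25, mean ratio exp((1.25² − 1)/2) = 1.32, n = 280: rank test 5%, Welch 50%.

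Skewness alone does no harm when both distributions have the same shape. The conflict appears when AID changes the spread as well as the level, which is plausible for a programme that adds cost for all and may avert a few expensive episodes.

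**The case against.** The strongest reply is that the text is narrower than the criticism. No rank test is named. The parametric branch compares means, and a non-parametric method could be the bootstrap, which the section itself names and which does address means. This stands in part: the mismatch belongs to the rank branch only. But the bootstrap is mentioned for the ICER, and a parametric or non-parametric choice made on skewness is ordinarily read as a t-type test or a rank test.

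A reader might infer that the ICERs themselves are invalid. The article does not support that, because bootstrap and Fieller both work on mean costs and effects. The mismatch affects the accompanying cost test.

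A reader might also infer that the plan knowingly compares sums over unequal time. It does not say so. The word total follows a description of multiplying volumes by prices and may mean summed over cost components. The fuller protocol may set a horizon. This stands, so the time-base point is conditional.

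Nor can an inflation of 37.5% or 56% be quoted as the size of the bias. Those ratios average group 1 in as zero usual-care months, although it contributes no usual-care cost after T0. Leaving it out of the usual-care mean lowers them to 1.10 and 1.22.

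Finally, a reader might infer that training costs are omitted. Economic evaluation names staff training as an investment that adds cost relative to usual care, so it is treated as a programme cost. What remains is only that the training month lies outside the 3-to-19-month follow-up windows.

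The simulation rates depend on assumed spreads and ignore clustering and residents who appear in both conditions. They show the direction of the problem, not its size in this trial.

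**Conclusion.** The concern holds in limited form. The skewness rule is stated, and its usual non-parametric branch does not test the mean cost difference on which the ICERs rest. The reported cost test and the ICER may therefore disagree in either direction. This conclusion rests on cost data being skewed and on the non-parametric branch meaning a rank test. How often they would disagree cannot be known from the article.

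The time-base point is separate and conditional. If totals per resident are not standardised, unequal time in each condition distorts the comparison towards higher AID costs by the ratios worked above. The article neither confirms nor excludes this. Because it links only the effect analysis to the design, allowance for unit and period in the cost comparison should be made explicit. The change is worth making, but the ICER uncertainty method is not undermined by the test rule.

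**What to change.** 1. Delete the skewness-dependent choice of test. Whatever the skewness, estimate and test the difference in arithmetic mean cost.
2. Express cost per resident-month, or per four-month interval, and account for unit and measurement period.
3. Take intervals from a method that respects clustering by unit and carries costs and effects jointly into the ICER, for example a multilevel model or a cluster bootstrap with a small-sample correction. Naive resampling of units within groups should be avoided. With 14 units in five groups there are 2 or 3 units per group, and such resampling shrinks between-unit variance by (n − 1)/n, to 1/2 or 2/3. With all 28 units pooled (5 or 6 per group) the factor is still 0.80 to 0.83.
4. Confirm that costs of the training month are counted under AID.

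The cost is revised wording, some extra programming and possibly wider intervals. No new data are needed.

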## Background

Depression is a common health problem in nursing home (NH) residents: prevalence rates vary from 6 to even 50% [1-3]. Depression is strongly related to quality of life of NH residents [4], it seriously impacts wellbeing and daily functioning, and increases use of health care services and even mortality [5-7]. The association between depression and quality of life highlights the importance of identifying and treating depression in NH residents with and those without dementia [8,4]. Unfortunately, although depression is a treatable disorder [9], various studies have shown poor detection and undertreatment of depression in NH residents [2,10-12].

Several studies have demonstrated effects of pharmacological and psychosocial interventions for depression in nursing homes [13,14]. The review of Bharucha et al. [15] of 'talk therapies' for depression in long-term care presents evidence for an improvement in depressive symptoms after reminiscence/life review therapy. Moreover, there is evidence for the effectiveness of multifaceted interventions in residential care [16-18] and in nursing homes [19,20].

The Nijmegen University NH Network (UKON), a collaboration between 12 care organizations and the Department of Primary and Community Care of the Radboud University Nijmegen Medical Centre, has developed the care program Act In case of Depression (AID), a multidisciplinary care program to identify and treat depression and monitor treatment effects. The care program is based on and in accordance with the recommendations as formulated in the Supplement Older Adults of the multidisciplinary evidence based guideline for diagnosis and treatment of depression [21] and the Consensus Statement of the American Geriatrics Society and the American Association of Geriatric Psychiatry [22]. The care program is an implementable plan of work that coordinates how the different disciplines should work together, fits in daily practice, and describes how new working methods are related to and can be integrated in the present care process following a step-by-step plan [23].

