### Sampling

We calculated the sample-size using the following assumptions.

For somatic units: 25 residents per unit [37], a depression prevalence of 22% [38], a remission rate of 40% [39], and an attrition of 20% [38].

For DSC units: 20 residents per unit [40], a depression prevalence of 30% [10,40-42], a remission rate of 35% [13], and negligible attrition [40].

Based on these assumptions and a significance level alpha of 0.05, a power of 0.80 and an ICC of 0.1 for both somatic and dementia residents, 14 clusters (units) with 6 measurements are needed in a stepped wedge design to allow multilevel analysis.

Given that the outcomes will be presented on unit-level, during the data collection, newly admitted residents and/or their legal representatives are asked to provide informed consent on all units. This way, the sample size is not influenced by death or relocation of participating residents and can remain stable.

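### QALYs taken from mean utilities in an open cohort, with no stated value for deaths, cannot register a survival difference

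*Protocol article*

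**What the plan says.** The Economic evaluation section of the protocol article sets two ratios: cost per percentage-point fall in depression frequency, and cost per QALY gained. For the second it states: "Using the trapezium rule, the QALYs will be computed in order to perform a cost-effectiveness analysis comparing the two alternative strategies". It then names the inputs. On the control side, "Change in utilities (EQ-5D) will be based on the mean values for the residents when they are in the control condition". On the intervention side it uses mean values after "3 (all 5 groups), 7 (4 groups), 11 (3 groups), 15 (2 groups) and 19 months (1 group". Costs, by contrast, are registered and totalled per resident.

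The Sampling section describes who supplies those values. "Given that the outcomes will be presented on unit-level", it says, "newly admitted residents and/or their legal representatives are asked to provide informed consent on all units" during the data collection, and in this way "the sample size is not influenced by death or relocation of participating residents and can remain stable". For somatic units it assumes 20% attrition, without giving a period or separating death from relocation. For dementia special care (DSC) units it calls attrition negligible.

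The Background says of depression that "it seriously impacts wellbeing and daily functioning, and increases use of health care services and even mortality".

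**The concern.** A QALY is utility accumulated over a person's time, with zero after death. Refilling places suits a prevalence measured on the unit, but it removes from the utility series the people whose lost time a QALY should count. If the means at 3, 7, 11, 15 and 19 months come from whoever is then present, a death leaves no direct trace in the area under them. It can act only indirectly, by changing who remains to be averaged.

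This affects the second economic question. A survival benefit or harm would not enter the denominator of the cost-per-QALY ratio. Even with equal survival, the gain is credited over time that some residents do not live. The two halves of the ratio also stop matching: a resident who dies contributes recorded costs up to death, but no QALY loss. Since the Background itself links depression to mortality, survival cannot be set aside as irrelevant.

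**Working it through.** **Whose exposure time is it?** Under Methods/Design, measurements T0 to T5 are 4 months apart. Group g (g = 0 to 4) starts after Tg, with one month of training first. Months in the intervention at measurement Tt are therefore 4t − (4g + 1).

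- g = 0: 3, 7, 11, 15, 19
- g = 1: 3, 7, 11, 15
- g = 2: 3, 7, 11
- g = 3: 3, 7
- g = 4: 3

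Counting groups at each time gives 5, 4, 3, 2 and 1, exactly the counts in the Economic evaluation section. The labels fit the unit's exposure.

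**Who is averaged?** Suppose the 20% somatic attrition is fully replaced. The share of newcomers at month m is 1 − 0.8^(m/P), where P is the period of the 20%.

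- P = 19 months: 3.5% at month 3 and 20% at month 19.
- P = 12 months: 5.4% at month 3 and 30% at month 19.

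The larger shares belong to month 19, which only one group reaches.

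**What the rule yields.** The documents give no utility or mortality figure, so the following are assumptions: control utility 0.5, constant over time, and all attrition treated as death. The trapezium rule is applied at 0, 3, 7, 11, 15 and 19 months.

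- Mean over residents present: 0.5 × 19/12 = 0.792 QALY, at any mortality.
- Deaths at 0, 20% over 19 months: the proportions alive are 1, 0.965, 0.921, 0.879, 0.838 and 0.800. The area under them is 1.419 years, and 0.5 × 1.419 = 0.710 QALY (10.4% lower).
- Deaths at 0, 20% a year: the proportions alive are 1, 0.946, 0.878, 0.815, 0.757 and 0.702. The area is 1.334 years, and 0.5 × 1.334 = 0.667 QALY (15.7% lower).

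**Effect on the difference.** Assume a utility gain of 0.05 among the living. The planned rule gives 0.05 × 19/12 = 0.079 in every case. With deaths at 0, the gain is 0.55 × (years alive, intervention) − 0.5 × (years alive, control). Years alive are 1.396, 1.334 and 1.273 at annual mortality of 15%, 20% and 25%.

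| Annual mortality, intervention / control | Planned rule | Deaths at 0 |
|---|---|---|
| 20% / 20% | 0.079 | 0.067 |
| 15% / 20% | 0.079 | 0.101 |
| 25% / 20% | 0.079 | 0.033 |

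With equal mortality the planned figure is 0.079/0.067, about 1.2 times the figure with deaths counted. If the 20% spans 19 months in both conditions, the gain is 0.05 × 1.419 = 0.071. The unequal-mortality rows show only that the error can go either way.

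**The case against.** The strongest reply is that the article does not say how deaths enter the QALY, and that a condensed article may leave this to the full plan. The stable-sample sentence concerns sample size and unit-level outcomes, not the scoring of utilities. This stands in part. A reader might infer that the plan excludes deaths outright. The text does not say so; it is the natural reading of means over a refilled sample. But the article does not leave the calculation open: it names the rule, the inputs, the times and the contributing groups. Followed as written, these give an area that deaths do not reduce.

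Several stronger readings are tempting and not supported:

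- *Trapezium on means is invalid in itself.* It is not. The rule is linear, so with fixed membership the area under the mean curve equals the mean of the individual areas. Only changing membership breaks this.
- *Labelling a recent admission with 19 months of exposure is an error.* The program is delivered to the unit through staff training and working plans, and units are randomized, so unit exposure time is a defensible index. No passage shows that a resident's own duration drives the effect.
- *The problem is equal across all 28 units.* DSC attrition is called negligible, and those are 14 of the 28.
- *The omitted survival component is a large, known share of the gain.* An assumed 3-point mortality difference over 19 months, with deaths spread evenly and utility 0.3 to 0.6, gives 0.03 × 0.5 × 19/12 × utility = 0.007 to 0.014 QALY. That is 22–45% of a sustained gain of 0.02 (0.032 QALY), but 9–18% of a gain of 0.05 (0.079 QALY). Neither the mortality difference nor either gain comes from the documents.

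It is also fair that survival is not a listed outcome, and that the economic section expects benefit through lower prevalence and saved staff time. That limits how likely a large survival effect is. It does not justify a rule that cannot show one.

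**Conclusion.** The point holds in a limited form. Means over a partly replaced population, with no stated value for deaths, give an area that does not fall with mortality. It is not a QALY gain in the sense of the cost-per-QALY question. With equal mortality the gain is overstated: 0.079 against 0.067 QALY at 20% annual deaths, or against 0.071 if the 20% spans 19 months. With unequal mortality the error can go either way.

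These sizes rest on an assumed utility gain of 0.05 and on treating all somatic attrition as death. Real losses include relocation, so the share due to death is smaller to an unknown degree. On the document's own figures the issue lies mainly in somatic units. It touches one of the two ratios and leaves the primary depression analysis and the sample size unaffected. The change is worth making before the economic analysis; it is not a flaw in the trial's main comparison.

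**What to change.** In the Economic evaluation section, replace the area under group means with QALYs per resident over each fixed 4-month measurement interval:

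- Use the resident's own EQ-5D values, with utility 0 from death to the end of the interval.
- Count residents who relocate up to their departure.
- Compare conditions per resident-interval in the planned multilevel framework, adjusted for period, because control time is earlier and intervention time later in this design.
- Sum costs over the same resident-intervals, so that both halves of the ratio cover the same people and time.
- Keep unit exposure time as the main index. Exposure counted from the resident's own inclusion can be a sensitivity analysis.

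If dates of death are not available, describe the result as a difference in mean utility among residents present and do not call it a QALY gain. If the full protocol already handles deaths this way, one clarifying sentence is enough.

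The cost is a little more analysis work and a need for dates of death and departure, which the article does not say are recorded. No new outcome measurement is needed. Two limits remain: time lost beyond the interval in which a death occurs is not counted, so deaths are only partly captured, and stopping at relocation may censor informatively.

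### The utility change behind the cost per QALY compares earlier control means with later intervention means, so any calendar trend in EQ-5D counts as programme effect

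*Protocol article*

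**What the plan says.** The Economic evaluation section of the protocol article defines the contrast used for QALYs. On the control side, "Change in utilities (EQ-5D) will be based on the mean values for the residents when they are in the control condition". On the intervention side it uses "the mean values after having been in the intervention for 3 (all 5 groups), 7 (4 groups), 11 (3 groups), 15 (2 groups) and 19" (exposure counted in months; the last value comes from one group). QALYs follow from these utilities: "Using the trapezium rule, the QALYs will be computed in order to perform a cost-effectiveness analysis comparing the two alternative strategies". The same paragraph opens with a general statement: "The effect analysis adheres to the design of the study".

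The layout is described under Methods/Design, around Figure 1: "each of the units is randomly assigned to one of 5 groups", and each group starts "directly after one of the measurements (T0-T4), which are each 4 months apart". Training takes the first month, so exposure at a measurement is 3, 7, 11, 15 or 19 months. By the end, "at the last measurement (T5), all 28 units are in the intervention condition".

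The Data-analysis section plans multilevel regression for the primary effects and names the EQ-5D as another primary outcome. Its listed covariates are age, sex, cultural background and cognitive status. It does not say that the estimate from this model feeds the QALYs.

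**The concern.** Condition and calendar time are tied together in this design: the share of control units falls from all at T0 to none at T5. A difference between a control-condition mean and an intervention mean therefore contains the programme effect plus whatever happened to EQ-5D between the two average dates. Possible sources are season, background change in care and changing case mix. Decline of individual residents counts only as far as new admissions do not offset it.

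The gap in dates also grows with exposure, so a steady trend would look like an effect that builds up with time in the programme. Cost-effectiveness is part of the study's stated aim, and cost per QALY is one of its two ratios. An error in the QALY difference passes straight into that ratio and the acceptability curve. The planned bootstrap or Fieller intervals describe sampling error and would not reveal it.

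**Working it through.** **Inputs from the article.** Five groups; measurements T0 to T5, 4 months apart (months 0, 4, 8, 12, 16, 20); group g starts after the g-th measurement. Equal group sizes are assumed.

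**The plan's own figure.** Enumerating the layout gives 5, 4, 3, 2 and 1 groups at 3, 7, 11, 15 and 19 months, as stated.

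**Average date of the control data.** Control groups number 5, 4, 3, 2, 1, 0 at T0 to T5:
(0×5 + 4×4 + 8×3 + 12×2 + 16×1) / 15 = 80/15 = month 5.33.

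**Average date of each intervention mean, and gap to the control mean.**

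| Exposure (months) | Measurements used | Mean month | Gap, pooled control | Gap, own-group control |
|---|---|---|---|---|
| 3 | T1–T5 | 12 | 6.67 | 8 |
| 7 | T2–T5 | 14 | 8.67 | 11 |
| 11 | T3–T5 | 16 | 10.67 | 14 |
| 15 | T4–T5 | 18 | 12.67 | 17 |
| 19 | T5 | 20 | 14.67 | 20 |

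The last column covers the other possible reading, in which each group is compared with its own control mean. Group g has control data centred on month 2(g−1).

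**False QALY difference with no true effect.** With a linear trend b in utility per year, the false utility change is b × gap/12. The trapezium rule runs over 0, 3, 7, 11, 15 and 19 months, with difference 0 at month 0.
- Pooled control: the areas are 10.00 + 30.67 + 38.67 + 46.67 + 54.67 = 180.67. Dividing by 144 gives 1.255 × b.
- Own-group control: 12 + 38 + 50 + 62 + 74 = 236. Dividing by 144 gives 1.639 × b.

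The values of b are assumptions, since the documents give none:

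| b per year | False utility change, 3 to 19 months (pooled) | False QALY, pooled | False QALY, own-group |
|---|---|---|---|
| -0.04 | -0.022 to -0.049 | -0.050 | -0.066 |
| -0.02 | -0.011 to -0.024 | -0.025 | -0.033 |
| 0 | 0 | 0 | 0 |
| +0.02 | +0.011 to +0.024 | +0.025 | +0.033 |

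**Scale against a real gain.** Assume a true utility gain of 0.03 from month 3 on, rising linearly from 0. The true QALY gain is 0.03 × (1.5 + 16)/12 = 0.0437. The pooled contrast would then give:
- b = -0.02: 0.0187, so the cost per QALY is 2.3 times too high for the same incremental cost.
- b = +0.02: 0.0688, so the cost per QALY is 0.64 of the true figure.
- b = -0.04: -0.0064, the wrong sign.

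**Does period adjustment remove it?** Fourteen units (3, 3, 3, 3, 2 per group) were simulated with a true effect of 0.03 and assumed utility SD 0.25, ICC 0.1 and 20 residents per unit. The overall raw contrast averaged -0.001, 0.015, 0.031 and 0.046 at trends of -0.04, -0.02, 0 and +0.02 per year. With unit and period in the model, the estimate was 0.029 to 0.030 throughout.

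**The case against.** The strongest defence is that the sentence only lists which measurements feed the QALY curve and leaves the model to the full plan. It does not say raw, pooled or unadjusted; the paragraph opens by tying the effect analysis to the design; and multilevel regression is planned for the EQ-5D. It is true that pooled is the natural reading and not an explicit one. But the specific sentence defines the change by means, nothing routes the regression estimate into the QALYs, and the own-group reading widens the gaps. The defence does not remove the problem.

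Some stronger readings are tempting but not supported:
- *The shrinking set of groups biases the effect.* Units are randomised to groups, so different composition is chance imbalance, not bias in expectation. What remains is imprecision: the 15- and 19-month means rest on two groups and one. The article discloses those counts.
- *Ageing and decline will drag the intervention means down.* The Sampling section describes continuing recruitment of newly admitted residents, which may keep the units' health mix fairly stable. No downward trend can be presumed.
- *The sign of the QALY result will be decided by drift.* This happens only under some assumed combinations of trend and true effect. At zero trend nothing is distorted.
- *The ratio per percentage point of depression has the same fault.* The article states no such means-based rule for that outcome.
- *The primary effect analysis is also unadjusted for time.* A period term not named in a condensed article may stand in the full plan; its absence from the covariate list is no finding in itself.

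**Conclusion.** The point holds for the QALY calculation. The utility contrast, as written, is confounded with calendar time under either reading of the control mean, by 6.7 to 14.7 months (pooled) or 8 to 20 months (own-group). With a pooled control mean, each 0.01 utility per year of background trend adds about 0.0125 to the QALY difference over 19 months, in the direction of the trend. A decline would understate the gain and an improvement would overstate it. The size rests on equal groups, a linear trend and a zero difference at month 0. The trend itself is unknown and may be nil. Separately, no control unit exists at T5, so the 19-month mean has no concurrent comparison.

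**What to change.** Replace the sentence that defines the change in utilities. State that the utility difference comes from the multilevel stepped-wedge model for the EQ-5D, with fixed effects for T0 to T5, a random unit effect and time since start of the intervention (3, 7, 11, 15, 19 months). Apply the trapezium rule to these period-adjusted differences and carry the result, with its uncertainty, into the cost per QALY and the acceptability curve. Mark the 19-month value as having no concurrent control, since it is then identified only through the model's assumptions.

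No extra data are needed. The cost is some analysis and programming work, and wider intervals once a separate effect is estimated for each exposure time, with least precision at 15 and 19 months.
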